## Abstract

**Background:**

Childhood obesity is the result of a long lasting imbalance between energy intake and energy expenditure. A major contributing factor is physical inactivity which is closely linked to bone health, cardiovascular disease risk, fitness and psychological factors. The school seems to provide an excellent setting to enhance levels of physical activity (PA). However, there is insufficient data from previous school-based intervention trials on how to enhance overall PA. It is also unknown whether an intervention aimed at increasing PA is effective in improving the children's health. The purpose of this paper is to outline the design of a school-based randomized, controlled trial (RCT) aiming to increase overall PA and to improve fitness and health in 6- to 13-year-old children.

**Methods/Design:**

15 schools were randomized to the intervention (n = 9) or the control (n = 6) group, stratified by geographic region (urban vs. rural) and by age (1^st ^and 5^th ^grade). Participation was given for all children in the intervention group since in this group the intervention was part of the normal school curriculum. The intervention during one academic year consisted of: 1. two additional physical education classes per week given by trained physical education teachers adding up to a total of five PA classes per week, 2. short PA breaks (2–5 min each) during academic lessons, 3. PA home work, and 4. adaptation of recreational areas around the school. All children underwent anthropometric measurements, blood pressure assessment, fitness testing, measurement of PA and they filled out questionnaires. At least 70% of all children agreed to blood sampling and measurements of body composition and bone mineral measurements by dual energy x-ray absorptiometry. The primary endpoints of the study after one year were an increase in total PA by accelerometry, an increase in aerobic fitness measured by the 20 m shuttle run, a decrease in percent body fat derived from skinfold measurements and an increase in quality of life as assessed by the child health questionnaire in the intervention group compared to the control group. Secondary outcomes were overall fitness, differences in body composition including body fat distribution, cardiovascular risk factors, psychosocial health, bone mineral content and density of femur, lumbar spine and total body and food intake.

**Discussion:**

Our preliminary data suggest that the children were representative of Swiss children with respect to sex, socio-demographic status, and body mass index. Short-term results can be expected by the beginning of 2007. We hypothesized that our intervention will lead to an increase in PA, fitness and overall health. Based on our data, we aim to provide important information regarding the influence of such an intervention on these outcome measures in school-aged children and to provide nationwide guidelines to improve PA in children.

## Background

### Initiation and realization of the research project

The debate regarding the ideal amount of physical education lessons that the state is ready to support is a major controversial issue in many countries, including Switzerland [1]. The importance of the growing problem of an inactive lifestyle in children, with the burden major health implications like obesity, type 2 diabetes, hypertension, low fitness and osteoporosis, is highly undervalued. The Swiss Federal Office of Sports (FOSPO) therefore decided to support an evaluation of the current level of physical activity (PA), fitness and health of elementary school children in Switzerland in addition to a school-based PA intervention program over the period of one academic year with a follow up three years later.

### Arguments for publishing a design paper

In this article we describe the design of a randomized controlled trial (RCT) assessing a school-based PA enhancing program which took place over the period of one school year. Publishing the design and rational of a RCT before the results are available has important benefits. The study can be critically evaluated for its methodological quality, irrespective of the results. If a design paper has been written, the results will most probably be published, even if the results are negative. A design paper includes a more detailed description of the study population, the intervention and all outcome measures than what can be reported in the method section of a regular publication focusing only on part of the study results. This paper will help researchers in the same field to compare the methods and the methodological qualities of future RCT and it provides detailed information for health professionals or educators to apply the intervention if the results show improvements in the outcome measures.

### Introduction

The increase in sedentary behavior, i.e. physical inactivity, over the last decades is thought to be one of the main risk factors for the development of obesity, diabetes, cardiovascular disease, osteoporosis and psychosocial constraints [2]. Despite widespread attempts to increase PA in the general population, only a minority of adults and children in developed countries engage in PA to a degree sufficient to maintain or increase health and physical as well as psychosocial well-being [3]. There is evidence that an insufficient amount of PA starts in childhood and tracks into adult life [4]. Risk factors which enhance sedentary behavior are large amounts of time spent in front of the television and/or computer, the inability to play outside or to actively commute to school, inactive parents or parents who do not support children to be active, and the lack of sufficient physical education at school. Although in children aerobic fitness is only moderately associated with PA, low PA and fitness are both associated with increasing prevalence of cardiovascular risk factors [5], even after adjusting for weight and/or obesity [5].

Currently, about 40–50% of the European adult population is overweight. Being overweight is an important risk factor for cardiovascular diseases, type 2 diabetes mellitus, musculo-sceletal disorders, and impaired quality of life [6]. The current epidemic of overweight and obesity is largely caused by an environment that promotes excessive food intake and discourages physical activity [7]. Even among children and adolescents, an alarming increase in overweight has been noticed. In 2002, the prevalence of overweight in 6- to 12-year-old Swiss children was 16.6 and 19.9% in boys and girls, respectively [8]. Even if obese adolescents become normal weight adults, they keep their burden of an increased cardiovascular risk [9]. Furthermore, there is a close link between (central) obesity and other cardiovascular risk factors like insulin resistance, hypertension, dyslipidemia and low-grade chronic inflammation in children and adolescents [5,10]. The prevalence of the metabolic syndrome has dramatically increased, and 46% of US adolescents have at least one risk factor of the metabolic syndrome [11]. Overweight children are also at increased risk to develop orthopedic complications and to suffer from stigmatization and discrimination [12].

PA does not only positively influence physiological factors, but has also a positive effect on psychological aspects. Fifty percent or even more of elementary school children report to be stressed or exhausted, and not able to sleep well [13]. Regular PA can increase the ability to cope with stress and leads to an improved health perception and quality of life [14]. In addition, a positive influence of PA on measures of anxiety and depressive symptoms [15] has been shown. PA does not only act on an individual level, but influences the school climate positively by increasing social competence within classes. This leads to an improved social behavior and more satisfaction with school, rated both by pupils and teachers [16]. Furthermore, regular PA can reduce substance abuse such as smoking [17]. Overweight children are particularly at increased risk to have a low self-esteem and to suffer from stigmatization and discrimination [12]. One report showed that the addition of regular PA lead to a higher self-esteem one year later in those children [18].

Maximizing bone mass during growth may constitute one of the most effective prevention strategies for osteoporosis, a disease which affects millions of people throughout the world. There is evidence that the degree of weight bearing activity and calcium intake is related to bone mass in childhood and adolescence [19,20]. Therefore, the benefits from PA in childhood may continue even into late adulthood [21].

Many school-based intervention studies promoting PA and a healthy lifestyle have been performed over the last two decades [22]. However, only a few studies documented increased PA during school-time [23,24]. In one study, even a reduction in out-of school PA as result of a PA program at school was observed [25]. In general, the results are disappointing, possibly due to methodological limitations, such as non-randomized trials, lack of objective measurements of PA and fitness, promotion of PA by non-experts and incomplete evaluation of cardiovascular risk factors [22,26]. In addition, a lack of overall increase in PA observed in many school-based intervention studies could be either due to compensation by increasing sedentary activity during out-of school time, or possibly due to the promotion of interventions that may not have been vigorous or sustained enough. A major advantage of interventions focusing on elementary school children is the relatively easy access through the schools, where changes in the school environment that promote healthy behaviors can be easier implemented and monitored, and can reach many schoolchildren of all social classes. Furthermore, the school environment gives the opportunity to work on various areas before, during and after school to increase overall and/or total PA.

## Methods/Design

### Study objectives

The aim of the proposed project was to evaluate in a RCT a school-based program if implementation of an extended PA program throughout the day during one school-year improved overall PA, physical fitness, physical health, and psychosocial well-being in 6- to 13-year-old children.

### Main outcomes

Primary outcomes of the intervention study were defined as

1. an increase in total PA measured by accelerometers,

2. an increase in aerobic fitness measured by the 20 m shuttle run test,

3. a reduction of percent body fat measured by skinfolds

4. an increase in quality of life measured by the child health questionnaire

in the intervention group compared to the control group.

Secondary outcomes of the intervention study were overall fitness (i.e. strength, speed, endurance, flexibility and coordination), body composition (including body fat distribution), cardiovascular risk factors (including blood pressure, blood lipids, glucose metabolism, C-reactive protein, adiponectin), bone health (including bone mineral content and density of femur, lumbar spine and total body as well as bone metabolism), psychosocial health (including social and stress coping, social anxiety, self esteem, drug abuse), and food intake. These outcomes were tested in different subgroups, i.e. 1^st ^vs. 5^th ^grade, girls vs. boys, children of different weight status, pubertal stages and socio-economic background.

### Study groups/Recruitment

Figure 1 shows the flow diagram of the recruited population. The study was performed in two provinces of Switzerland. Within these provinces, there were 919 elementary schools. Of these 95 fulfilled our stratification criteria, i.e. rural versus urban localization, and a prevalence of 10–30% children from other ethnicities. These strata were chosen in order to be representative for the Swiss population. Recruitment of participating schools (i.e. cluster randomization) was based on the willingness of these 95 elementary schools to be randomized either to an intervention group with a PA curriculum or a control group. Fifty percent of all children were in 1^st ^grade (6–8 years), and the other children were in 5^th ^grade (10–12 years) with evenly distributed gender. Fifteen schools with a total of 27 classes were randomized by a random-number table. Sixteen classes in 9 schools located in 6 communities were randomized to the intervention group (INT), and eleven classes in 6 schools in other communities of the same provinces were randomized to the control group (CON). A higher number of schools in the INT than in the CON group, i.e. a randomization ratio of 3:2 was chosen to gain more experience with the intervention and to reduce costs of the trial. Data of the INT and CON group were collected solely in the schools, in order to minimize the absence time from the usual school curriculum due to travelling.

Although the intervention program itself was established as part of the school curriculum for all children in the INT group, informed consent for the questionnaires and all measurements was necessary for all participants and was given by the children and a parent. The study was approved by the Ethics Committees of the University of Basel, the University of Zürich, as well as by the cantonal ethical committee of Aargau, Switzerland.

### Data analysis

To compare the success of randomization, descriptive statistics were used to compare the baseline measurements of the two groups. The primary analysis was a comparison of the change of the primary and secondary outcome factors between the intervention and the control group following the "intention to treat" principle. Initial power analysis was based on a two-sided t-test on the pre-post changes in the primary outcome measures (total PA, aerobic fitness, percent body fat, quality of life), with adjustments to account for the intraclass correlation (ICC) due to cluster randomization by school. The study was powered to detect a medium effect size on all primary study outcome measures of 0.5 units of standard deviation with 79% power if the ICC was 0.10 and with 90% power if the ICC was 0.06. Sample size required to reach the estimated power was a total of 360 children at the third measurement, four years after baseline assessment. Assuming an attrition rate of 10–15% and accounting for the multiple secondary outcomes, we recruited 530 children in the intervention and control group to provide adequate power to test/challenge the following null-hypothesis of the study: At the end of the intervention there will be no difference in the primary outcomes between the intervention and the control groups. Pre-planned subgroup analyses will be performed for age groups (1^st ^vs. 5^th ^grade), gender, weight status, pubertal stage, and socio-economic background. Where appropriate, adjustments were made for differences in baseline values. The same differences in the outcomes will be also tested 3 years later.

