Our trial has some limitations. First, despite the randomization of intervention and control schools, the children, parents and classroom teachers knew the group allocation prior to baseline testing which could bias test results. This was unavoidable, as the time schedule and organization of the school year in the intervention groups had to be adapted several months before the school year started. Second, some of the investigators were not blinded to group assignment of the children because of the extensive need of manpower for testing and the financial restraints to recruit additional, blinded personnel. To assess some of the variables, we did not exclusively use validated measures. For example, we modified some of the questionnaires regarding PA or food intake to better adapt to our local situation and to broaden some of the information. Regarding PA, we will validate the questionnaires against the accelerometer measurements both before and after the intervention. Regarding the food questionnaire, we think that it is more informative to adapt them to the local use, especially as the gold standard, i.e. a 3–7 dietary recall protocol by itself has many shortcomings. PA has various effects on multiple determinants of health. We therefore defined several primary outcomes to be able to measure all important aspects related to an increased PA which we intended to induce by our intervention.

We hypothesize that our intervention will lead to an increase in PA, fitness and overall health. Should we be able to confirm these hypotheses, implementation of the PA promotion program throughout Switzerland and in other countries will help to improve health and fitness of our school children with the obvious potential of reduced direct (health care) and indirect (work absenteeism and productivity) costs later in life.

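### Four primary outcomes share one null hypothesis with no stated alpha, success rule or family-wise control, and the extra children recruited for the secondary outcomes do not limit type I error

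*Protocol article*

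**What the plan says.** The Main outcomes section of the protocol article lists four primary outcomes without ranking them: total physical activity, shuttle-run fitness, percent body fat from skinfolds, and quality of life.

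In Data analysis, the power calculation rests on a "two-sided t-test on the pre-post changes in the primary outcome measures (total PA, aerobic fitness, percent body fat, quality of life", adjusted for clustering by school. It targets a "medium effect size on all primary study outcome measures of 0.5 units of standard deviation", with 79% power at ICC 0.10, 90% at ICC 0.06, and 360 children.

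One null hypothesis covers all four outcomes: "At the end of the intervention there will be no difference in the primary outcomes between the intervention and the control groups".

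Multiplicity comes up once in the same section, as a reason for the recruited number: "accounting for the multiple secondary outcomes, we recruited 530 children in the intervention and control group". The other reason given is attrition of 10–15%.

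The Discussion explains why there are four: "We therefore defined several primary outcomes to be able to measure all important aspects related to an increased PA". It gives no rule for combining them. No significance level, order of testing or success rule appears anywhere in the article.

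**The concern.** A single null over four outcomes needs a rule saying what rejects it. There are two natural rules, and each has a consequence that the plan does not address.

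- **Any one outcome suffices.** Four unadjusted tests then give a false-positive rate well above the level of each test.
- **All four must be positive.** Type I error is then controlled without splitting alpha, but the stated power applies to one outcome at a time and the chance of overall success is much lower.

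The one multiplicity provision is directed at the secondary outcomes and consists of more children. A larger sample does not change the type I error of an unadjusted test. It could pay for a stricter alpha, but none is stated. The four primary outcomes get no provision at all. If the rule is chosen after the results are known, it will carry little weight.

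**Working it through.** **Inputs.** From Data analysis: four outcomes, effect 0.5 SD, ICC 0.10 or 0.06, 360 children, attrition 10–15%, 530 recruited. From Study groups/Recruitment: 15 schools, 9 intervention and 6 control, allocation 3:2. Assumed, because the article does not state it: 0.05 two-sided per test. Correlation between outcomes is also not given, so a range is shown.

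**1. The plan's own power.** With 216 and 144 children, each school has m = 216/9 = 144/6 = 24. The design effect is 1 + (m − 1) × ICC, which is 3.30 at ICC 0.10 and 2.38 at ICC 0.06. The standard error is √[design effect × (1/216 + 1/144)], or 0.1954 and 0.1660. Dividing 0.5 by these gives 2.558 and 3.013. Normal-approximation power at 0.05 is Φ(2.558 − 1.960) = 72.5% and Φ(3.013 − 1.960) = 85.4%. A noncentral t with 15 − 2 = 13 df gives 65.8% and 79.5%. The stated 79% and 90% are therefore not reproduced at 0.05; by the normal approximation they would need a two-sided alpha of about 0.08.

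**2. Any one of four, 0.05 each, no true effects.** If the outcomes are independent, 1 − 0.95⁴ = 18.5%. Simulating equicorrelated normal statistics (1,000,000 draws) gives 17.4% at correlation 0.3, 15.5% at 0.5 and 13.0% at 0.7. With 0.0125 per test, 1 − 0.9875⁴ = 4.9%.

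**3. All four required.** Taking the stated per-outcome power at face value and assuming independence, 0.79⁴ = 39% and 0.90⁴ = 66%. Positive correlation would raise these, at most to 79% and 90%.

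**4. Power at the Bonferroni level.** The two-sided critical value at 0.0125 is 2.498, so power is Φ(2.558 − 2.498) = 52% and Φ(3.013 − 2.498) = 70%. For 360 children in 15 schools:

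| Two-sided alpha | ICC 0.10, normal | ICC 0.10, 13 df | ICC 0.06, normal | ICC 0.06, 13 df |
|---|---|---|---|---|
| 0.05 | 72.5% | 65.8% | 85.4% | 79.5% |
| 0.0125 | 52% | 40% | 70% | 56% |

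The fair comparison for the cost of adjustment is between these two rows, not with 79% and 90%.

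**5. What the extra children buy.** Attrition alone takes 360 to 360/0.90 = 400 or 360/0.85 = 424, so 530 − 424 = 106 to 530 − 400 = 130 children are left to be attributed to the secondary outcomes. After attrition, 530 becomes about 450 to 477. With 15 schools, the effective sample (N divided by the design effect) rises from 109 to 115–117 at ICC 0.10 and from 151 to 164–168 at ICC 0.06. That is a modest gain in power and no change in type I error.

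**The case against.** The strongest reply is that much of this is silence in a condensed design article, and that a multiplicity procedure may sit in an analysis plan that is not shown. That is a fair limit, and silence alone would not be a finding. But the article does state one null over four outcomes and a power claim for each of them, and it answers multiplicity in a way that leaves out the primary outcomes. Those statements need correcting whatever another document contains.

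Four stronger readings are tempting, and the text does not support them.

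- **That each outcome is powered or tested at the full 0.05.** No alpha is printed, and it cannot be recovered from the power figures. They do not reproduce at 0.05 with 15 schools. They come close at 0.025 if the 27 classes are taken as clusters (80.9% and 90.1% with 360 children), although the article says the adjustment was for schools.
- **That one positive outcome would reject the null and support national implementation.** The wording of the null could be read that way, but the Discussion makes implementation depend on confirming its hypotheses, in the plural. The rule is left open.
- **That the t-test is the analysis.** The sentence presents it as the basis of the initial power calculation. The primary analysis is described only as an intention-to-treat comparison of changes.
- **That the authors claim the 530 controls type I error.** They justify it by adequate power. The valid criticism is narrower: as an allowance for multiple outcomes it does nothing about false positives.

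It can also be argued that four distinct constructs, each reported separately, need no family-wise control. That is a defensible choice, but it has to be stated, and it fits poorly with a single joint null.

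**Conclusion.** The concern holds in this form: four co-primary outcomes stand under one null, each powered separately, with no alpha, success rule or family-wise control. The only multiplicity allowance is sample size for the secondary outcomes.

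Its size depends on the rule that is missing. With any-of-four success at an assumed 0.05 per test, the family-wise error is about 13% to 19% for correlations from 0.7 to 0. With all-four success there is no inflation, but joint power is about 39% or 66% under independence. Neither outcome is what a reader would take from the stated 79% and 90%.

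The failure of those two figures to reproduce at 0.05 with 15 schools is a separate issue and should not be counted as a cost of multiplicity.

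**What to change.** Before the outcomes are analysed, add one paragraph to the analysis plan that does the following:

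1. Sets an overall two-sided 0.05 for the four primary outcomes and declares success per outcome under Holm's procedure. The alternative is a fixed sequence in the order of the Main outcomes section (total physical activity, shuttle run, percent body fat, quality of life), each tested at 0.05 only if the one before it is significant.
2. Labels the secondary outcomes as supportive and unadjusted.
3. Stops presenting the 530 as accounting for multiple outcomes, and describes it as a margin for attrition and precision.
4. Restates power under the chosen rule, using the 15 schools at 9:6.

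The cost is a stricter threshold and a lower stated power. The 0.0125 row of the table is the worst case for Holm, since it is the first step; later steps are less strict. A fixed sequence keeps 0.05 for the first outcome, but a non-significant result on total physical activity would block claims on the other three. No change to recruitment or measurement is needed.

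### At an assumed two-sided 5% level, the stated 79% and 90% power does not match 360 children in 15 schools split 9:6, and the inputs behind it are not given

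*Protocol article*

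**What the plan says.** All of this is in the protocol article.

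- **Method (Data analysis).** "Initial power analysis was based on a two-sided t-test on the pre-post changes in the primary outcome measures", with "adjustments to account for the intraclass correlation (ICC) due to cluster randomization by school".
- **Power (Data analysis).** The effect and power are "0.5 units of standard deviation with 79% power if the ICC was 0.10 and with 90% power if the ICC was 0.06", claimed for all primary outcomes.
- **Sample size (Data analysis).** "Sample size required to reach the estimated power was a total of 360 children at the third measurement, four years after baseline assessment". The recruited number is explained separately: "Assuming an attrition rate of 10–15% and accounting for the multiple secondary outcomes, we recruited 530 children in the intervention and control group". The null hypothesis that follows concerns the end of the intervention, not the third measurement.
- **Design (Study groups/Recruitment).** "Fifteen schools with a total of 27 classes were randomized by a random-number table": 9 schools (16 classes) to intervention and 6 schools (11 classes) to control. On allocation, "a randomization ratio of 3:2 was chosen to gain more experience with the intervention and to reduce costs of the trial".

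The article does not state the significance level, the number of clusters assumed or the cluster size assumed.

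**The concern.** With school as the unit of randomisation, power depends mainly on the number of schools. The article prints both a power claim adjusted for school and the number of schools, so the two can be compared. On conventional assumptions they disagree, and the printed power is the more favourable.

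A reader who takes 79–90% at face value would treat a null result on a primary outcome as stronger evidence against a half-SD effect than 15 schools can supply.

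**Working it through.** **Inputs from the article.** Effect d = 0.5 SD; ICC 0.10 and 0.06; N = 360; 15 schools, 9 and 6; two-sided t-test; clustering by school.

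**Assumptions.** Two-sided alpha 0.05 (not stated) and equal school sizes, so m = 360/15 = 24 children per school, and n1 = 9 × 24 = 216, n2 = 6 × 24 = 144.

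**Formulae (SD units).** DEFF = 1 + (m − 1) × ICC. SE = √[DEFF × (1/n1 + 1/n2)]. Normal-approximation power = Φ(d/SE − 1.960). The t version uses the noncentral t with noncentrality d/SE on 15 − 2 = 13 df.

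**Step 1: try to reproduce the stated figures with the randomised design.** 1/216 + 1/144 = 0.01157.

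| ICC | DEFF | SE | d/SE | Normal | t, 13 df | Stated |
|---|---|---|---|---|---|---|
| 0.10 | 1 + 23 × 0.10 = 3.30 | 0.1954 | 2.558 | 72.5% | 65.8% | 79% |
| 0.06 | 1 + 23 × 0.06 = 2.38 | 0.1660 | 3.013 | 85.4% | 79.5% | 90% |

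The stated figures are not reproduced. The shortfall is about 5–7 points by the normal method and 10–13 points on 13 df.

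**Step 2: use the children available at the end of the intervention.** 530 × 0.85 = 450 and 530 × 0.90 = 477. The design is the same 15 schools, 9:6.

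| Children | ICC 0.10, t to normal | ICC 0.06, t to normal |
|---|---|---|
| 450 | 68.2–74.9% | 82.7–88.1% |
| 477 | 68.8–75.4% | 83.4–88.7% |
| 530 (no loss) | 69.7–76.4% | 84.6–89.7% |

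At ICC 0.10 every entry is below 79%. At ICC 0.06 the normal method comes close to 90%; the t version does not.

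**Step 3: find the source of the shortfall.** 15 schools in equal halves (360 children) give 74.3% (normal) and 67.6% (t) at ICC 0.10, and 86.8% and 81.1% at ICC 0.06. Compared with Step 1, the 9:6 split costs 1.8 points at ICC 0.10 and 1.4–1.6 points at ICC 0.06. The rest comes from the small number of schools.

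**Step 4: look for inputs that would give the stated figures (360 children).**

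| Variant | ICC 0.10 | ICC 0.06 |
|---|---|---|
| 17 clusters, equal arms, normal, alpha 0.05 | 78.0% | 89.1% |
| 18 clusters, equal arms, normal, alpha 0.05 | 79.5% | 90.0% |
| 19 clusters, equal arms, normal, alpha 0.05 | 81.0% | 90.8% |
| 18 clusters, 3:2, normal, alpha 0.05 | 77.9% | 88.8% |
| 15 schools, 9:6, t on 13 df, two-sided alpha 0.10 | 78.1% | 88.6% |
| 27 classes as clusters, 16:11, alpha 0.05, t to normal | 85.0–87.7% | 92.4–94.2% |

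Several variants come within about 2 points of both figures. Treating the classes as clusters overshoots.

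**Step 5: detectable effect.** At 360 children, ICC 0.10 and 79% power, the normal method gives (1.960 + 0.806) × 0.1954 = 0.54 SD. The noncentral t on 13 df gives 0.58 SD. The article says 0.5 SD.

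**The case against.** **The significance level is assumed.** The article never states it. At two-sided 10% with t on 13 df, the actual 9:6 design gives 78.1% and 88.6%, near both stated figures. A reader might infer that the stated power is unobtainable from this design; that is too strong, and the mismatch holds at two-sided 5%. Nothing in the article suggests a 10% level, though, and if one was used it needed stating.

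**The calculation behind the figures is unknown.** Because 18 equal clusters of 20 fit so closely, a reader might infer that the calculation was made for that design, with equal allocation and class-sized clusters. The article gives no assumed cluster number or size, and Step 4 shows that other configurations also fit. The close match is no diagnosis.

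**The 360 belongs to the third measurement.** The null hypothesis concerns the end of the intervention, when more children should remain. This stands in part: at ICC 0.06 the normal method then gives 88–89%, close to the claim. At ICC 0.10 the gap remains at 75% at best. So 66–73% and 80–85% should not be read as the trial's power without qualification.

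**Recruitment of 530.** A reader might infer an arithmetic error because 360 inflated for 10–15% attrition is 400–424, or because a fall from 530 to 360 is 32%. The article does not support that inference. It gives the multiple secondary outcomes as a second reason for 530, and it presents 360 as a required minimum, not a forecast. Recruiting above a minimum is no error.

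**It is labelled an initial power analysis, and the trial is under way.** That may explain how the figures arose, but the article still presents them as the study's power, next to a design that does not yield them at 5%.

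**Conclusion.** The concern holds in a limited form. Assuming two-sided alpha 0.05 and equal school sizes, 360 children in 15 schools (9:6) give 66–73% power at ICC 0.10 and 80–85% at ICC 0.06, not 79% and 90%. The lower end of each range is t on 13 df, the upper end the normal approximation. The claim at ICC 0.10 is missed for any number of children up to the 530 recruited; the claim at ICC 0.06 is nearly met at the end of the intervention, but only by the normal method. Unequal school sizes would lower all of these: with an assumed coefficient of variation of 0.3, 360 children give 63–70% and 77–84%.

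The article does not allow the inputs behind its figures to be recovered, so the finding is a mismatch between the power statement and the randomised design. It does not identify how the mismatch arose.

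**What to change.** In Data analysis, state the significance level, the number and average size of clusters, and the method (normal approximation, or t with df from the number of schools). Replace the power sentence with figures for the randomised design at both time points. If two-sided 5% is confirmed, the entries are:

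- 360 children at the third measurement: 66% (t, 13 df) or 73% (normal) at ICC 0.10; 80% or 85% at ICC 0.06.
- 450–477 children at the end of the intervention: 68–69% (t) or 75% (normal) at ICC 0.10; 83% or 88–89% at ICC 0.06.
- Detectable effect at 360 children, ICC 0.10 and 79% power: 0.58 SD (t) or 0.54 SD (normal).

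Use one named method throughout. If another significance level was used, state it and recompute at that level.

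The cost is rewording. At two-sided 5% the stated power becomes less favourable. Design, analysis and recruitment do not change.
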